## Abstract

**Background:**

Unhealthy lifestyles in early childhood are a major global health challenge. These lifestyles often persist from generation to generation and contribute to a vicious cycle of health-related and social problems. This design article presents a study evaluating the effects of two novel healthy school interventions. The main outcome measure will be changes in children’s body mass index (BMI). In addition, lifestyle behaviours, academic achievement, child well-being, socio-economic differences, and societal costs will be examined.

**Methods:**

In close collaboration with various stakeholders, a quasi-experimental study was developed, for which children of four intervention schools (*n* = 1200) in the southern part of the Netherlands are compared with children of four control schools (*n* = 1200) in the same region. The interventions started in November 2015. In two of the four intervention schools, a whole-school approach named ‘The Healthy Primary School of the Future’, is implemented with the aim of improving physical activity and dietary behaviour. For this intervention, pupils are offered an extended curriculum, including a healthy lunch, more physical exercises, and social and educational activities, next to the regular school curriculum. In the two other intervention schools, a physical-activity school approach called ‘The Physical Activity School’, is implemented, which is essentially similar to the other intervention, except that no lunch is provided. The interventions proceed during a period of 4 years. Apart from the effectiveness of both interventions, the process, the cost-effectiveness, and the expected legal implications are studied. Data collection is conducted within the school system. The baseline measurements started in September 2015 and yearly follow-up measurements are taking place until 2019.

**Discussion:**

A whole-school approach is a new concept in the Netherlands. Due to its innovative, multifaceted nature and sound scientific foundation, these integrated programmes have the potential to form a template for primary schools worldwide. The effects of this approach may extend further than the outcomes associated with well-being and academic achievement, potentially impacting legal and cultural aspects in our society.

**Trial registration:**

The study protocol was registered in the database ClinicalTrials.gov on 14-06-2016 with the reference number NCT02800616.

## Background

Unhealthy lifestyles, bred by low levels of physical activity and unhealthy dietary behaviours, are a persistent problem in Western societies [1]. Such lifestyles are usually adopted at a young age, and often persevere into adulthood [2]. Even in early childhood, unhealthy behaviours contribute to major issues such as a reduced health-related quality of life (HR-QoL), psychosocial problems, and chronic diseases including obesity [3–5]. In the long run, this often results in higher health care costs, reduced academic achievement, reduced labour participation, and a lower socio-economic status (SES) [5, 6]. A vicious circle is likely to emerge, transferring problems from one generation to the next. It is clearly a major challenge for public health professionals to break this tenacious pattern.

In efforts to reverse the public health epidemic, the school setting is an ideal environment for promoting healthy lifestyles. A school setting enables multiple aspects of health promotion (education, social environment, physical environment, school health policy, parenting) to be modified, thereby facilitating successful implementation [7]. For instance, the school setting offers the advantages of facilitating compliance with an intervention and also enables preventive measures to reach children from a variety of socio-economic and ethnic backgrounds [8, 9]. The Dutch primary school system in particular, leaves much room for improvement with respect to nutrition, and physical activity during the school day [10]. In addition, there is some preliminary evidence that lifestyle interventions improve academic achievements, thereby helping schools to achieve their primary academic goals [11–13].

Worldwide, many school-based health interventions have been evaluated [14]. Over 80 % of these interventions reported at least one positive effect on risk factors for non-communicable diseases (e.g. obesity, physical inactivity, smoking, inadequate or poor nutrition) [15]. Despite the relatively high costs of school-based interventions, existing programmes have been found to be cost-effective in terms of body mass index (BMI) improvements and HR-QoL gains [16, 17]. Normalized BMI distributions, gathered across the entire school population, provide an informative outcome measure for the evaluation of such interventions. Newly learned healthy lifestyle habits are likely to lead to favourable weight changes among overweight and obese children, as well as underweight children, but are also likely to stimulate children with a healthy weight to maintain their weight. Admittedly, the potential of school-based interventions to normalize BMI is found to be modest [14, 15, 18]. The most frequently reported reasons for this modest effectiveness are low parental involvement, a short duration of the intervention, and a lack of a whole-school approach [14, 15, 18–21]. It is often considered difficult to acquire the necessary support and deal with the high costs and efforts that need to be made to implement multicomponent interventions. As a result, schools often choose less intense single-component interventions. Physical education seems to be one of the most viable components to effectively decrease obesity rates in schools [20, 22]. Despite the implementation benefits of single-component interventions, however, a whole-school approach should always be preferred, as newly acquired lifestyle habits are more likely to last if embedded within an integrated approach.

We present a study protocol that examines the effectiveness of two novel, integrated healthy school interventions. One is a full intervention called ‘The Healthy Primary School of the Future’, the other is a partial intervention called ‘The Physical Activity School’. These intervention approaches will be compared with the regular school approach that is currently common practice in the Netherlands. We hypothesize that these healthy school interventions will result in normalized BMI distributions that are more in line with national and international standards (smaller standard deviations) among primary school children, with a more pronounced effect in the full intervention schools (due to the expected synergy between exercise and diet) than in the partial intervention schools. Also, our multi-disciplinary research group will study a wide range of outcome measures, including lifestyle behaviours, academic achievement, child well-being, socio-economic differences, and societal costs. Moreover, an evaluation will be performed of the legal consequences of a healthy school approach in the Netherlands, as well as the conflicting interests of the stakeholders.

Our primary research question is: What is the effect of the full intervention (‘The Healthy Primary School of the Future’) on the BMI of primary school children compared to no intervention (control schools)? Our secondary research question is: What is the effect of the full intervention on the BMI of primary school children compared to the partial intervention (‘The Physical Activity School’)?

Our tertiary research questions are: (1) What is the effect of the full intervention in comparison with the partial intervention and the regular school approach (control schools) on: (a) children’s levels of physical activity and sedentary behaviour, nutritional knowledge, healthy food preferences and behaviour, cognitive and non-cognitive performance, HR-QoL, socio-emotional development, and sick leave? (b) parenting and teacher practices regarding physical activity and nutrition? (c) parental HR-QoL, well-being, labour participation and sick leave? (d) benefits across different socio-economic backgrounds? (e) long and short term cost-effectiveness? (f) satisfaction among the involved stakeholders (children, parents, teachers, and child care partners)? (2) Which determinants influence the quality of the implementation of the intervention? (3) What is the scope of children’s human rights to health, what is the legal role of primary schools in realizing these rights (e.g., obligations and responsibilities of state and non-state actors, conflicts of interests and legal solutions to these conflicts), and is the intervention feasible within Dutch educational law?

## Methods

### Setting and study design

The current study has a quasi-experimental design with four intervention schools and four control schools. All participating schools are primary schools situated in the Parkstad region in the Province of Limburg, in the southern part of the Netherlands. This is a relatively poor region with a low SES in which unhealthy lifestyles are highly prevalent [23, 24]. Overweight and obesity rates are substantially higher than the national average in the Netherlands [25]. The intervention schools and control schools are both members of the MOVARE educational board. In the Dutch primary school structure, pupils successively follow eight ‘groups’, starting in group 1 at the age of 4 and typically proceed to secondary school at the age of 11 or 12. Internationally, the first two groups are comparable to pre-school and the last six groups are comparable to grades 1–6.

Two schools take part in the full intervention named ‘The Healthy Primary School of the Future’. Two other schools implement the partial intervention named ‘The Physical Activity School’ (Fig. 1). No randomization was applied, because full voluntary cooperation and participation of the intervention schools is required for the implementation of the interventions. The population consists of a dynamic cohort comprising children in groups 1–8 (Table 1). Baseline measurements were conducted in September-October 2015, and yearly follow-up measurements will take place until 2019. The intervention started in November 2015.

**Fig. 1 Fig1:**
[figure not shown]
Study design

**Table 1 Tab1:** Dynamic study cohort

Cohort	T1 2015/2016	T2 2016/2017	T3 2017/2018	T4 2018/2019	T5 2019/2020	Exposure in years
A					Group 1	0
B				Group 1	Group 2	1
C			Group 1	Group 2	Group 3	2
D		Group 1	Group 2	Group 3	Group 4	3
E	Group 1	Group 2	Group 3	Group 4	Group 5	4
F	Group 2	Group 3	Group 4	Group 5	Group 6	4
G	Group 3	Group 4	Group 5	Group 6	Group 7	4
H	Group 4	Group 5	Group 6	Group 7	Group 8	4
I	Group 5	Group 6	Group 7	Group 8	Group 8 ^a^	4
J	Group 6	Group 7	Group 8			3
K	Group 7	Group 8				2
L	Group 8					1

^a^In cohort I, T5 measurements will be conducted in June 2019 instead of September -November 2020

Almost all schools in the southern part of the Netherlands participate in the health monitoring programme of the regional Public Health Services (GGD) and the OnderwijsMonitor Limburg, a collaboration between Maastricht University, schools and school boards to collect data from children at school in Limburg [26, 27]. This allows us to put the measures of this intervention into the perspective of the total school population of the wider Limburg region.

### Recruitment of schools and subjects

#### Recruitment of intervention schools

In March 2013, 12 out of 53 schools governed by the MOVARE educational board were informed about the study. These schools were selected because of their supportive geographical environment (e.g., sufficient sports facilities in the area and supportive local politicians). Out of these 12, we aimed to recruit four large intervention schools with a minimum of 140 children per school in groups 2, 3, 4 and 5. Four schools gave their initial consent and started to raise support from all stakeholders (e.g., parents, children, partners of the school) and to develop the intervention together with partners. Eventually, two of the four schools gave their approval for the full intervention. A third school received enough support from stakeholders to implement the partial intervention and a fourth school dropped out because of a lack of support among school staff and parents. After the withdrawal of this school, another school from the same educational board was recruited to implement the partial intervention. The recruitment of all intervention schools was completed in July 2015.

#### Recruitment of control schools

From all schools of the MOVARE educational board, four control schools were recruited with a minimum of 140 children per school in groups 2, 3, 4 and 5. All schools that voluntarily agreed to participate could join the study, and no inclusion or exclusion criteria were set. The recruitment of the control schools was completed in January 2015. The control schools are characterized by a school environment that is representative of schools in the Netherlands in terms of lifestyle education, school hours and number of physical education (PE) classes.

The intervention and control schools are comparable in terms of socioeconomic status and there are no statistically significant differences in academic performance, as measured at baseline by the so-called CITO scores (see the section on Children's academic achievements).

#### Recruitment of subjects

The recruitment of the children for the baseline measurement was completed in October 2015. Until 2019, all new children entering the intervention and control schools will be invited to participate in the study (Table 1). For the baseline measurement, children were recruited by means of information brochures sent by mail, and reminders by the school staff. In addition, the research team visited all classrooms to inform children about the study and to encourage them to participate. All children of the intervention and control schools are eligible to participate in this study (Table 1). Children who switch schools during the four-year study period will not be followed up with the extensive measurement programme, but we do have the outcome variables collected by the OnderwijsMonitor Limburg and GGD for these children.

### Interventions

The interventions are based on the socio-ecological approach to school health promotion, focusing on the wider picture of interrelationships between individuals with their personal characteristics (e.g., children and their parents), and their environment (e.g., the school and its neighbourhood) [7]. The interventions focus on multiple aspects (education, social environment, physical environment, school health policy, parental practices) and aim to influence multiple settings (school, home environment, school neighbourhood).

Both school interventions, ‘The Healthy Primary School of the Future’ and ‘The Physical Activity School’, involve making changes to school hours and physical activity. School hours are extended to facilitate implementation of the interventions. Children attend school from 08:30 to approximately 15:30/16:00 instead of 8:30 to 12:30 and 13:30 to 15:00. These school hours allow educational activities to be more in line with children’s bio-rhythm [28]. Where possible, schools use the 10:00–12:00 and 14:00–15:30/16:00 time-slots for cognitive tasks, as previous studies suggest that children can concentrate better during these timeframes than during those used in regular school environments [28]. With regard to physical activity, the schools offer a structured programme including sports, play and creativity for at least 1 hour a day for 4 days a week, guided by the pedagogical staff (Table 2).

**Table 2 Tab2:** Compulsory changes and possible additional activities to promote a healthy lifestyle

Theme	Situation of control schools	Compulsory changes	HPSotF	PAS	Additional activities in HPSotF and PAS
School hours	➢ 08:30–14:30/15:00	➢ 08:30–15:30/16:00	X	X	
	Obligatory lessons. Lunch break for lunch from school 30–60 min.	Obligatory lessons. Lunch break and organised sports, free play and cultural activities of 75–90 min.			
School health policy	➢ No school health policy.				Changing existing policy into healthy lifestyle stimulating policy.
Healthy lifestyle education	➢ No nutritional and/or physical activity education.				➢ ‘Lekker Fit’ program: healthy lifestyle education with physical activity and nutrition lessons as part of the curriculum [60].
Physical activity	➢ 30-min lunch break with free play.	➢ Organised sport, free play and cultural activities of at least 60 min a day.	X	X	➢ ‘By Foot And By Bike’ program: between-class competition focusing on active transport.
	➢ 1 h PE/week.				➢ Energizers: introducing short breaks of physical activity during lessons.
	➢ No physical activity breaks.				➢ Increased intensity of PE lessons [61].
	➢ School yard with limited physical activity stimulating facilities.				➢ At least 2 PE lessons a week
					➢ Introducing swimming lessons.
					➢ Schoolyard with a physical activity stimulating environment.
					➢ Introduction lessons by sports clubs.
Nutrition	➢ Children eat foods brought along from home at school or they have lunch at home.	➢ Healthy lunch and morning snack provided by school.	X	-	➢ ‘Smaaklessen’ program: practical food tasting lessons [62].
					➢ Keeping a vegetable garden at the school yard.
					➢ Distribution of water bottles.
Socio-emotional well-being	-				➢ ‘Taakspel’ program: a group-based approach in which children learn to comply better with rules in the classroom [63].
Parents	-				➢ Website with general advice for healthy practices at home.
					➢ ‘Gezonde afspraken met je kind’: e-health program to make healthy agreements with one’s child.
					➢ ‘Goedkoop Gezonde Voeding’ program: learning about cheap and healthy nutrition.
					➢ Interactive theatre: interactive evening to discuss (obstacles of) healthy practices at home.
					➢ ‘COOL’ program: lifestyle intervention for overweight children and their parents
					➢ ‘Lifestyle Triple P’ program: lifestyle intervention for parents of overweight children.

*Abbreviations*: *HPSotF* healthy primary school of the future, *PAS* physical activity school, *PE* physical education

The full intervention schools provide a healthy morning snack and healthy lunch every day. Lunch is provided in the classroom or in a central location in the school. A variety of food products from all food groups are available, from which children can choose. The products are carefully selected to meet the guidelines of the Netherlands Nutrition Centre Foundation. Pedagogical staff will supervise the lunch sessions to make sure that the children choose products from all recommended food groups and that they choose the recommended portion sizes. The lunch cycle changes every 10 weeks.

In addition to these compulsory implementations, both the full and the partial intervention schools can choose to offer additional activities (Table 2). To support and encourage the schools, we searched for relevant and evidence-based additional activities, using a systematic health promotion approach, based on the PRECEDE-PROCEED model [7, 29] and the Intervention Mapping protocol [30]. A diagnosis of the health problems (step 1) and associated behavioural and environmental factors (step 2) resulted in behaviour goals, e.g. children using active transport to school and children eating two pieces of fruit a day. We also searched the literature for determinants that influence these behaviour goals (step 3). Next, the resulting overview of determinants was used to search for evidence-based activities or best practices available nationally or internationally (step 4) [31]. Schools are free to choose the activities which best fit their possibilities and goals. Employees of the regional Public Health Services (GGD) and community sports coaches support stimulate the school in this decision-making process.

Additional activities focus on school health policy. Creating policy on health topics, for example on healthy birthday treats, should clarify what social norms are important to the school, making the communication with parents easier and more consistent. Additional activities also focus on health education. A healthy lifestyle education programme is expected to promote healthy nutrition (fruit, vegetables, fibre-rich products, lower fat and lower sugar products and normalized portion sizes), physical activity (reduction of sedentary behaviour, increase in moderate- to high-intensity physical activities, compliance with the Dutch standards for healthy behaviour), and socio-emotional well-being (increased self-esteem, executive control function, decreased bullying). The educational activities incorporate interactive lessons, and games to increase knowledge of, and familiarity with, healthy food products and physical activities. Schools intend to set aside at least 1 hour per week in the school curriculum for health education.

Additional activities are implemented with the aim of creating an optimal social and physical environment to make healthy choices easier. For instance, schools can choose to increase PE classes and/or increase the intensity of the existing PE classes. The schoolyard can be equipped with low-cost facilities to encourage physical activity, such as play equipment and balls. Sports clubs can be introduced to the schools to give introductory lessons to the children. Short physical activity breaks can be incorporated during lessons in order to reduce sedentary time. These breaks can occur in the classroom (e.g. games involving physical movements, interactive dances), or outside in the schoolyard. Regarding nutrition, the schools are stimulated to choose additional activities such as food tasting, gardening (i.e., growing vegetables), and the distribution of water bottles.

Finally, several additional activities are aimed at parents to stimulate parental involvement and encourage the successful transfer of a healthy lifestyle from school to home.

### Outcome measures

An overview of all outcome measures and the corresponding informants (e.g., child, parent, teacher, or other) is presented in Table 3. All measurements will be completed yearly unless stated otherwise. Measurements involving the children will be obtained in groups, during regular classes, except for the anthropometric measurements. All questions will be tailored to the different age categories and include numerous graphical illustrations. No open-ended questions will be used. All questionnaires have been pretested several times in comparable populations and settings. In the youngest groups (groups 2–4), the questions will be read out by the teacher or a research assistant, and answered in writing by the children. The oldest children (groups 5–8) will read and fill in the questionnaires themselves. During the completion of the questionnaires, a teacher and at least one researcher will be present to monitor the process and to answer questions. The majority of the child-related measurements will be scheduled during one regular school week to avoid overburdening the children and school staff. Children in group 1 will be excluded from most measurements, as their young age (4 years in September) complicates most of the measurements. Also, not all group 1 children will attend school yet during the measurement periods (September-October), as children in the Netherlands gradually enter group 1 during the school year, depending on their birthday. Parents of children in groups 1–8 will receive an online questionnaire and teachers of all classes will receive a short questionnaire on paper. Privacy-sensitive questions, such as parental BMI, SES and disease status will not be mandatory to complete.

**Table 3 Tab3:** Overview of all the outcome measurements and their corresponding sources

Outcome measurement	Informants					
	Children			Parents of children in groups 1–8 (age 4–12)	Onderwijs monitor Limburg	GGD
	Group 2 (age 5–6)	Group 3–4 (age 6–8)	Group 5–8 (age 8–12)			
General health child						
Weight, objectively measured	X	X	X			
Height, objectively measured	X	X	X			
Waist and hip circumference, objectively measured	X	X	X			
Handgrip strength, objectively measured	X	X	X			
Blood pressure						X
Disease status, hospital admissions, medicine use, healthcare visits				X		X
Sick leave					X	
Birthweight						X
Socio-emotional health of child						
HR-QoL (EQ-5D-Y, PedsQL)			X	X		
Psychological attributes (SDQ)			X	X		
Self-efficacy (SEQ-C and Manikin scale, full SEQ-C only in groups 7–8)			X			
Self-confidence, social skills, school wellbeing, future expectations and social support					X	
Physical activity behaviour of child						
Physical activity (Actigraph)		X	X			
Sedentary behaviour (ActivPal)			group 5			
Shuttle run test		X	X			
Sports club membership		X	X	X		
Active transport forms to school	X	X	X			
Leisure time physical activity	X	X	X			
Leisure time physical activity				X		
Dietary behaviour of child						
Food intake (food frequency questionnaire and dietary recall)	X	X	X	X		
Familiarity with healthy food products	X	X	X	X		
Food preferences	X	X	X	X		
Household information						
Parental weight and height				X		
Parenting styles						X
Parenting practices regarding nutrition and physical activity (CSPQ)				X		
Parental well-being (SWLS)				X		
Parental HR-QoL (EQ-5D)				X		
Parental labour participation				X		
SES (including deprivation, income, and education)				X		
Parental leave and absence due to illness of child				X		
Teacher-related variables						
Teacher’s practices regarding nutrition and physical activity					X	
Teacher’s height and weight					X	
School achievement of child						
Test results (CITO and other tests)					X	
School advice and secondary school track actually attended					X	
Learning disabilities					X	
School absenteeism and repeating years					X	
Process-evaluation						
Qualitative and quantitative evaluation	X	X	X	X		
New school entries					X	

*Abbreviations*: *CITO* centrale eindtoets basisonderwijs, *CSPQ* comprehensive snack parenting questionnaire, *EQ-5D-Y* EuroQol 5-Dimensions Youth version, *EQ-5D* EuroQol 5-Dimensions, *GGD* regional public health services, *PedsQL* paediatric quality of life inventory, *SDQ* strength and difficulties questionnaire, *SEQ-C* self- efficacy questionnaire for children, *SWLS* satisfaction with life survey

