#### Teacher-related variables

Teacher’s self-reported weight and height and transport forms to work are assessed by means of a written questionnaire. School practices regarding nutrition and physical activity (e.g., modelling eating healthy food products and encouraging children’s physical activity) are determined by an adapted version of the Parental Practices Instrument.

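### In groups 2–4 either the class teacher or a research assistant may read out the child self-report questions, so delivery is not standardised and could favour intervention schools after baseline

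*Protocol article*

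**What the plan says.** Outcome measures sets out how the child questionnaires are given.

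- **Groups 2–4:** "In the youngest groups (groups 2–4), the questions will be read out by the teacher or a research assistant". The replies are "answered in writing by the children".
- **Groups 5–8:** "The oldest children (groups 5–8) will read and fill in the questionnaires themselves".
- **All groups:** "a teacher and at least one researcher will be present to monitor the process and to answer questions".

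The same section says that there are no open-ended questions, that items carry many illustrations, and that the questionnaires were pretested.

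Table 3 lists food intake, familiarity with healthy foods, food preferences, active transport and leisure-time activity for children from group 2, and sports club membership from group 3. Under Background these outcomes fall within the tertiary research questions.

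On allocation, Setting and study design states: "No randomization was applied, because full voluntary cooperation and participation of the intervention schools is required for the implementation of the interventions". On self-report error, the Discussion relies on comparing differences over time with multilevel methods.

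**The concern.** The article does not fix who reads. It permits the class teacher even though a researcher is in every session. The teacher in an intervention school may not be neutral. The article treats teachers' own conduct as something to be measured, including "modelling eating healthy food products and encouraging children’s physical activity" (Teacher-related variables). Intervention schools intend weekly health education in the curriculum, and activity breaks may be held during lessons (Interventions). Table 2 describes control schools as having no nutrition or activity education.

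A child of about 5 to 8 who hears a question on fruit, lunch or cycling from a teacher who promotes those things may lean towards the favoured answer. If that happens more in intervention schools, and only once the programme is running, it would look like a programme effect on diet or activity behaviour. With two schools per intervention arm, the practice of one school could move an arm's mean.

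**Working it through.** The article gives no figure for reader effects, so there is none to reproduce. The check sets the sections side by side.

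**1. Does the analysis remove such an error?** The tertiary numerical outcomes use the same mixed model as the primary outcome, with group, time and group*time (Data analysis for primary and secondary, and for tertiary, research questions). For read-out children, write for arm *a* at wave *t*:

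- p(a,t) = share of sessions read by a teacher;
- δ(a,t) = average shift towards healthier answers when a teacher reads rather than a researcher.

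The part of the group*time contrast that comes from the reader is

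[p(I,t)·δ(I,t) − p(C,t)·δ(C,t)] − [p(I,T1)·δ(I,T1) − p(C,T1)·δ(C,T1)].

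This is zero if the shift and the share of teacher readers are the same in both arms, or if the difference between arms stays constant over time. It is not zero if δ rises in intervention schools after the November 2015 start, because baseline was measured in September–October 2015. It is also not zero if p changes differently by arm, which the open choice of reader allows. Setting p = 0 everywhere removes the term. The article states neither p nor δ.

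**2. What share of children is affected?** Group 1 is left out of most measurements, which leaves groups 2–8, seven year groups. Groups 2–4 are 3/7 = 43% of year groups. With equal group sizes, a net shift of δ in groups 2–4 adds at most 0.43·δ to an all-group mean, and that only if teachers read every intervention session. If teachers never read, it adds nothing.

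**3. Which cohorts are read to, and when?** From Table 1:

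| Cohort | Waves in groups 2–4 |
|---|---|
| F | T1, T2, T3 |
| G | T1, T2 |
| H | T1 |
| I | none |
| E | T2, T3, T4 |
| D | T3, T4, T5 |
| C | T4, T5 |
| B | T5 |

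Cohorts F–I, on which the sample size rests (Table 4), have 4 cohorts × 4 follow-up waves = 16 follow-up cells. Three of these are read out (F at T2 and T3, G at T2): 3/16 = 19%, and none at T4 or T5. At T5 only the later entrants B, C and D are read to.

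**4. Which outcomes have another source?**

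- BMI comes from measured weight and height.
- Actigraph data start at group 3.
- Parents also report food intake, familiarity, preferences, sports club membership and leisure activity.
- Group 2 has no Actigraph measure in Table 3, so its activity data rest on reports alone.
- Lunch recall is asked in class straight after lunch. Parents are a second informant on diet but do not see a lunch eaten at school. Lunch recall in the full-intervention schools is therefore the most exposed item.

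**The case against.** The strongest reply is that the article already limits prompting. The teacher is one of two permitted readers, the children write their own answers to closed and illustrated questions, and a researcher monitors each session. This stands. A reader might infer that school staff collect the dietary and activity outcomes, but the text does not support that.

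A reader might also infer that the class teacher delivers the intervention. The document names other staff for the compulsory parts. The activity programme is "guided by the pedagogical staff", and for lunch "Pedagogical staff will supervise the lunch sessions to make sure that the children choose products from all recommended food groups". Classroom components are optional. That a teacher has a stake is a reasonable inference, not a stated fact.

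Researchers and research assistants are not stated to be blinded, and children know their own school's programme. Some socially desirable answering would therefore remain whoever reads. A familiar voice may also help the youngest children understand the questions. Both points stand, and they limit what the change can achieve.

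It can also be said that a condensed article leaves scripts and session logs to a field manual. That is fair for the script itself. The choice of reader, however, is a rule that the article states, and it states it as open.

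Finally, the Discussion acknowledges self-report error and says that the process evaluation will be used to assess potential bias. Acknowledging the error does not remove one that differs by arm and begins after baseline.

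**Conclusion.** The point holds as a limited, avoidable risk of differential reporting. It rests on two assumptions that the document makes plausible but does not establish: that teachers in intervention schools have some stake in the programme, and that this stake, or the mix of readers, changes differently between arms after baseline. Bias could then arise; the document does not show that it will.

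Its reach is tertiary child-reported outcomes in groups 2–4: three of seven year groups, and 3 of 16 follow-up cells in cohorts F–I. Its size cannot be derived from the document.

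Three stronger readings are not supported:

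- It does not threaten the primary or secondary BMI comparisons, the Actigraph data or the parent reports.
- The 43% is a share of year groups, not of child questionnaires. Several instruments, such as those on quality of life and self-efficacy, are asked of children only in groups 5–8.
- The four-year contrast in cohorts F–I has no read-out at follow-up.

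**What to change.** Baseline is complete, so the change applies to the remaining waves. In Outcome measures, replace the open choice of reader by a rule to this effect: in all eight schools, the questions in groups 2–4 are read out by the research team member present, from the same script; the teacher keeps order and helps with practical matters; who read is recorded for each session, and for baseline sessions where it is known. The record would show whether the reader differed by arm or wave.

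Teachers need not be barred from answering every query in all groups. That would be more of a trade-off, especially where only one researcher is present, and this point does not require it.

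The cost is small, because at least one researcher is already planned for every session. The downside is a less familiar reader for the youngest children, equally in all arms. The gain is standardised delivery without the teacher's stake. The article should not describe the result as blinded collection.
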